**Methods:**

We aim to recruit 66 cervical dystonia patients into a double-blind comparison of pallidal neurostimulation versus botulinum neurotoxin type A. Eligible patients need ≥25% motor symptom reduction 4 weeks after a neurotoxin test injection, but are willing to undergo DBS surgery due to unsatisfactory symptom control. All participants will be implanted with a DBS system, and randomized into 2 groups: First group will receive effective neurostimulation and saline injections into dystonic muscles. Second group is treated with regular neurotoxin injections and undergoes a sham-stimulation. Primary outcome is the change in TWSTRS total score between baseline and 6 months of therapy. Secondary outcome parameters are corresponding changes in TWSTRS motor score, Tsui score, CDQ-24 and SF-36. Safety will be assessed by frequency and severity of reported adverse events. Statistical analysis includes intention-to-treat and per protocol populations, analysis based on imputation of missing values and analysis adjusting for differences in baseline TWSTRS. After 6 months of blinded treatment all patients will receive open-label neurostimulation and neurotoxin treatment as needed, and are followed up 48 weeks after randomization.

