Deep brain stimulation (DBS) is a surgical therapy for movement disorders, which retunes abnormal neuronal activity within motor circuits by continuous electrical stimulation of deep brain nuclei. DBS requires the surgical implantation of stimulating electrodes connected to a pacemaker device. There is class I evidence for the safety and efficacy of DBS applied to several brain targets (subthalamic nucleus, internal globus pallidus (GPi) and thalamus) for patients with Parkinson’s disease (PD) [8], tremor disorders [17] and dystonia [12]. Treatment effects of DBS are strong and can lead to almost complete symptom suppression even in severely disabled patients. Nevertheless, this therapy has been restricted to advanced disease stages after failure of pharmacological treatment alternatives out of principle safety considerations. DBS surgery carries a risk of permanent morbidity and mortality resulting from intracranial haemorrhage or infections, while the treated conditions are disabling but not life limiting by themselves. Otherwise, DBS may come too late in advanced disease stages for restoring function and societal participation in chronically disabled patients despite being effective on a symptom level. Improved surgical techniques and perioperative management have now reduced the chronic morbidity and mortality risk of DBS below 0.5% [11], which has allowed considering earlier DBS with the goal to maintain function and prevent psychosocial decline in PD. For example, the EARLYSTIM trial [16], a controlled randomized comparison of subthalamic DBS with best medical management of PD with early motor fluctuations has established superiority of DBS for improving off-period symptoms, response fluctuations and quality of life. Interestingly, there was no difference in the total number of AE and serious AE between both treatment groups over the 2 year study period, suggesting that the risks associated with medical treatment or inappropriate symptom control of PD have been largely underestimated in the past and may be mitigated by DBS.

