**Fig. 1 Fig1:**
[figure not shown]
Visit schedule of StimTox-CD: SCR = screening visit, EVA = evaluation visit, DBS = DBS surgery, RAN = randomization visit, FU = follow-up visit, icon “syringe” ≙ BoNT or placebo injection, icon “reflex hammer” ≙ clinical assessment, icon “operating room” ≙ DBS surgery, icon “lightning” ≙ DBS setting/sham stimulation

**Table 1 Tab1:** Eligibility criteria

Inclusion criteria	Exclusion criteria
• Suffering from isolated, idiopathic or hereditary cervical dystonia for more than 2 years • Moderate to severe symptom severity of dystonia (TWSTRS total score ≥ 20 points and TWSTRS motor score ≥ 15 points) • Age between 18 and 75 years • Adequate therapy response of BoNT A treatment during test injection procedure (≥ 25% reduction of points in TWSTRS motor score 4 weeks after baseline) • Previous BoNT injection ≥12 weeks before screening visit • Written informed consent to study participation, including patient’s agreement to undergo DBS procedure	▪ Mild dystonic symptoms (TWSTRS total score < 10 points and TWSTRS motor score < 5 points) ▪ Suffering from severe depression with ongoing suicidality (BDI > 25 points) ▪ Mild cognitive impairment (MCI) and dementia (MDRS ≤125 points) ▪ Ongoing acute psychosis ▪ Drug or alcohol abuse ▪ Pregnancy or lactation, women of childbearing age without secure contraception ▪ Illiteracy ▪ Surgical contraindication to DBS ▪ Concurrent participation in other clinical trials ▪ Any medical or psychological condition associated with the risk of insufficient compliance and/or early termination of the study

All participants undergo stereotactic implantation of deep brain electrodes in GPi under general anaesthesia. Comparable to previous dystonia DBS studies, the applied neurostimulation system is ACTIVA PC (MEDTRONIC, Minneapolis, USA), including matching electrodes 3387 and 3389 [13, 19]. DBS procedure depends on local standards in each study centre. There are no detailed specifications on perioperative management and stereotactic procedure. Only a preoperative MRI-scan (including T1-, T2, gadolinium-enhanced and inversion recovery sequences) in general anaesthesia and a postoperative image control of electrode positioning are mandatory.

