6 (±1) weeks after DBS implantation patients are divided in two study arms during “randomization visit” (RAN). Table 2 is showing the full data set, which is collected at RAN as baseline for the upcoming blinded study phase. Neurostimulation will be now activated for the first time and acute stimulation effects and adverse effects of all electrodes are tested in a structured fashion (“monopolar review”). In DBS group a local DBS expert implements an effective stimulation setting concerning stimulation amplitude and choice of electrodes after “best clinical practice” and a predetermined algorithm. Frequency must be adjusted to 130 Hz, pulse duration to 90 μs. In BoNT group stimulation amplitude is set to 0 V. This group is injected with BoNT by an experienced physician. The decision on preferred drugs (Onabotulinumtoxin A: BOTOX, Abobotulinumtoxin A: DYSPORT or Incobotulinumtoxin A: XEOMIN), applied dosage and injection technique (number of injections, injection site or guiding-techniques) is up to the discretion of the treating physician and supposed to correspond to best clinical practice. During the same visit, patients in DBS group get also injected, but only with saline. Neither patient nor treating physician is informed about the allocation to the study group, in the sense of a double-blind trial design. Obviously DBS setting is not appropriate to be implemented in a blind manner, what causes the need of two separate teams of physicians at each study site; one blinded (or BoNT) and one unblinded (or DBS) team.

**Table 2 Tab2:** Synopsis of interventions and data sets (displayed for single SimTox-CD study visits)

	Screening visit/SCR	Evaluation visit/EVA	DBS surgery/DBS	Randomization visit/RAN	Follow-up visit 1/FU1	Follow-up visit 2/FU2	Follow-up visit 3/FU3	Follow-up visit 4/FU4	Follow-up visit 5/FU5
timeline (weeks)	−14 (+/−1)	− 10 (+/− 1)	−6 (+/− 1)	0	+4 (+/− 1)	+ 12 (+/− 1)	+ 16 (+/− 1)	+ 24 (+/− 1)	+ 48 (+/− 1)
Interventions									
BoNT test injection	X								
DBS surgery			X						
Testing of stimulation (side) effects				X					
DBS setting/sham stimulation^a^				X		X			
Blind BoNT/placebo injection^a^				X		X			
Unblind neurostimulation								X	X
Randomization				X					
Data set									
Informed consent	X								
Inclusion/exclusion criteria	X	X							
Medical history	X								
Concurrent medication	X				X	X	X	X	X
TWSTRS	X	X		X	X	X	X	X	X
Tsui Rating Scale	X	X		X	X	X	X	X	X
Bain Tremor Rating	X	X		X	X	X	X	X	X
GCI	X	X		X	X	X	X	X	X

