CDQ-24	X			X				X	X
SF-36	X			X				X	X
EQ-5D	X			X				X	X
MDRS	X			X				X	(X)
BDI	X			X				X	(X)
BPRS	X			X				X	(X)
Video recording	(X)	(X)		X	(X)	(X)	(X)	X	X
Questionnaire on DBS procedure			X						
Postoperative control of electrode position				X					
AE					X	X	X	X	X
DBS settings				X	X	X	X	X	X

^a^according to randomized group allocation

Abbreviations (in alphabetical order): *AE* adverse events, *BoNT* Botulinum neurotoxin, *BDI* Beck Depression Inventory, *BPRS* Brief Psychiatric Rating Scale, *CDQ*-24 Craniocervical Dystonia Questionnaire, *DBS* deep brain stimulation, *EQ-5D* Euroquol (life quality questionnaire), *GCI* Global Clinical Impression Scale, *MDRS* Mattis Dementia Rating Scale, *TWSTRS* Toronto Western Spasmodic Torticollis Rating Scale, *SF*-36 Short Form 36 (life quality questionnaire)

4 (±1) weeks after randomization first follow-up visit (FU1) is scheduled. Clinical outcome parameters are evaluated by blinded physicians. The same procedure is repeated during FU2 and FU3 (12 (±1) and 16 (±1) weeks after RAN), with a second blindly applied BoNT or placebo injection. In FU2 also adjustments of DBS settings are allowed to improve neurostimulation effect in DBS group. The blinded study phase ends in FU4, 24 (±1) weeks after randomization. Neurostimulation is now activated also in BoNT group and the open trial phase starts. Up from FU4, patients are treated commonly without restrictions concerning DBS programming or BoNT injection, treatment must basically conform again to best clinical practice. During FU5, after another interval of 24 (±1) weeks, study ends and a last detailed clinical assessment is intended.

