The primary statistical analysis of the primary outcome parameter as well as the secondary outcome parameter change in TWSTRS motor score, TSUI score and SF-36 score will be based on the intention-to-treat (ITT) population. To proof robustness of results two further analyses of sensitivity will be performed: the first one refers to all randomized patients with imputation of missing values after 6 months by appropriate methods of missing-data imputation depending on which missing-data mechanism could be reasonable. The second method includes only patients of per protocol (PP) population.

To address the question how much TWSTRS total score values differ between DBS and BoNT group on average, when patients would be start at baseline with the same score values, we will use ANCOVA (target variable: TWSTRS total change score from baseline to 6 months after operation, main factor: treatment method, covariate: baseline TWSTRS). Thereby we will adjust to imbalances in the TWSTRS distributions at baseline and the variance within the groups should be reduced.

Also for secondary outcome parameters an ANCOVA will be applied using treatment group as main factor, adjusted for each baseline variable as covariate. Furthermore longitudinal data of scores will be analysed by using GEE (generalized estimating equation) and linear models (“mixed models”). This will be helpful to describe interindividual variability of therapy response.

Safety analysis contains a structured list of AE of both study groups. Possibility of relation to study’s interventions will be judged by physicians of the unblinded team. Incidence of AE will be assessed by using Fisher’s Exact Test (analysis by patients: comparisons of proportions of patients with at least one corresponding event) and negative binomial regression (analysis by events: comparisons of counts of occurring events).

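### The planned between-arm adverse-event tests compare two implanted groups, and AE collection is scheduled only from FU1, so they cannot support the aim of showing that DBS is safe

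*Protocol article*

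**What the plan says.** **Timing of surgery and randomisation.** The Abstract (Methods) states: "All participants will be implanted with a DBS system, and randomized into 2 groups". The Study protocol section adds: "All participants undergo stereotactic implantation of deep brain electrodes in GPi under general anaesthesia", and "6 (±1) weeks after DBS implantation patients are divided in two study arms". The next scheduled contact is FU1: "4 (±1) weeks after randomization first follow-up visit (FU1) is scheduled".

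**AE schedule.** The AE row of Table 2 is marked at FU1 to FU5. It is blank at screening, evaluation, DBS surgery and RAN. The only data item marked in the surgery column is the "Questionnaire on DBS procedure", whose content and analysis the article does not describe.

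**Safety analysis.** Outcome measures has AE frequency and severity measured in the two treatment arms, from spontaneous reports. Statistics says: "Safety analysis contains a structured list of AE of both study groups". It then compares the proportions of patients with an event (Fisher) and the event counts (negative binomial).

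**Risk and aim.** The Background locates the serious risk in the operation: "DBS surgery carries a risk of permanent morbidity and mortality resulting from intracranial haemorrhage or infections". The Abstract sets out to demonstrate that DBS is safe in partial toxin responders, and the Perspective section hypothesises the same. The end of the Background says only that safety will be explored.

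**The concern.** The choice facing a future patient is surgery plus stimulation, or toxin without surgery. The trial randomises between active stimulation plus saline and toxin plus sham stimulation, in people who have all had the surgery. That is a sound way to blind the efficacy comparison, but it takes the operation out of the safety comparison.

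Two features add to this. First, arms exist only from RAN, so a patient whose complication prevents randomisation is in neither group. Second, followed as written, Table 2 does not prompt for AEs at the two visits closest to the operation.

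At stake is the claim that DBS can be offered earlier, which the Summary makes conditional on DBS proving safe in this indication. Balanced AE counts between the arms would say nothing about the hazard that the Background names.

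**Working it through.** **1. Numbers available.** The article gives no figure for safety. Its sample size is 28 per arm for the primary outcome, with 15% drop-out: 28 / 0.85 = 32.9, so 33 per arm and 66 randomised. This reproduces and is unaffected by the present point. The screening figure also reproduces: 66 / (0.8 × 0.8) = 103.1, stated as 104. It allows for refusal of DBS and for test-injection failure, but not for patients lost between implantation and randomisation.

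**2. Time from surgery to the first scheduled AE entry.** 6 (±1) weeks to RAN plus 4 (±1) weeks to FU1 is 10 weeks, range 8 to 12.

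**3. Can the arm comparison show implantation harm?** Let the surgical risk be s. Surgery precedes allocation, so the expected risk is s in both arms and the expected difference is s − s = 0. The probability that Fisher's test gives p < 0.05 at 33 per arm, by exact enumeration over assumed values of s:

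| Surgical risk s, both arms | Probability of rejection |
|---|---|
| 0.5% | < 0.0001 |
| 5% | 0.002 |
| 10% | 0.012 |
| 20% | 0.024 |

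These are false-positive rates, not power. A larger surgical risk does not make it detectable, and complete recording from the day of surgery would not change that.

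**4. What the arm comparison can show.** The BoNT arm is set to 0 V until FU4, so stimulation-related harms can differ between arms in that period. From FU4 both arms are stimulated, and events up to FU5 no longer contrast stimulation with sham.

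**5. Effect of mixing surgical events into the arm test.** Assume true stimulation-phase risks of 30% and 5%. Power at 33 per arm is 0.70. If an independent surgical event risk s is counted in both arms, each risk becomes 1 − (1 − s)(1 − p):
- s = 20%: 1 − 0.8 × 0.70 = 44% against 1 − 0.8 × 0.95 = 24%; power 0.31.
- s = 50%: 65% against 52.5%; power 0.14.

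The risks are illustrative. The direction does not depend on them: common events dilute the one contrast that the test can address.

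**6. What a single cohort could show.** With zero events in 66 implanted patients, the exact 95% upper limit is 1 − 0.025^(1/66) = 5.4% two-sided, or 1 − 0.05^(1/66) = 4.4% one-sided. At a true risk of 0.5% the chance of seeing any event is 1 − 0.995^66 = 28%. These figures follow from n = 66, not from the AE schedule, and would be the same after the fix. They bear only on the word *demonstrate*. The Background's 0.5% is an upper bound on chronic morbidity and mortality, so it is a reference value here, not a perioperative AE rate.

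**The case against.** **Events may be captured elsewhere.** Table 2 is captioned as a synopsis in a journal article. Spontaneously reported AEs need not be tied to a visit box, and an FU1 entry can look back. The surgery questionnaire, the postoperative electrode check or AE rules in the full protocol may pick up perioperative events. This stands. A reader might infer that six perioperative weeks go unrecorded, but the document supports only that AE collection is not scheduled then. The blank cell at RAN still needs explaining, because the text presents Table 2 as the full data set collected at that visit.

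**Not all DBS harm cancels.** Correct: stimulation effects differ between arms until FU4. Only implantation and hardware harms have equal expected rates.

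**Timing of complications.** One might add that most haemorrhages and infections occur before FU1. The Background names these events but gives no timing, so the point does not rely on it.

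**Safety is secondary, and no equivalence is claimed.** No safety margin is set, AEs are listed after the secondary outcomes, and the structured AE list would show any recorded surgical event in a randomised patient. All true. But the list is also organised by study group, so it omits the never-randomised, and the Abstract and Perspective still go beyond exploring.

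**Implanting both arms and unblinded causality.** Double implantation is a disclosed price of blinding, and nothing here asks to change it. That relatedness to the "interventions will be judged by physicians of the unblinded team" might also look like a flaw. That team knows the stimulation settings, and who judges first is a design preference, so it is not part of this point.

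**Conclusion.** The point holds for the between-arm tests. For harms of implantation and hardware their expected difference is zero by design. With 33 per arm, Fisher's rejection probability stays at or below 0.024 across the surgical risks tried (0.5% to 20%). A non-significant result is therefore not evidence that DBS is safe, and the stated aim outruns the analysis.

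This rests on two premises in the document, implantation before randomisation and AE analysis by study group. It also assumes that hardware harms after randomisation do not depend on whether stimulation is on. It does not rest on perioperative events being lost. Whether they are captured is an open question that the blank cells in Table 2 raise and the article does not settle. The primary efficacy analysis and the sample size are untouched.

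**What to change.** 1. In Table 2, mark AE/SAE collection in the DBS surgery and RAN columns. If the full protocol already requires it, correct the table to say so.
2. Report surgery- and device-related events in all implanted patients, including those never randomised, as one cohort with incidence and exact 95% confidence intervals.
3. Limit the between-arm AE tests to RAN–FU4 and describe them as active stimulation plus saline versus toxin plus sham stimulation, in implanted patients. Report events after FU4 descriptively.
4. Align the safety wording of the Abstract and Perspective with the end of the Background: safety is explored or estimated, not demonstrated.

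The cost is an earlier AE page in the case report form, one additional table and some rewording. No visits, staff or patients are added. Item 1 is best settled before patients are implanted, because events not collected prospectively may not be fully recoverable later.

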## Perspective

StimTox-CD is the first multicentre, randomized, double-blind and sham-controlled trial of DBS vs. best conservative therapy, specifically selective peripheral denervation with BoNT in CD patients, which have a partial treatment effect of ongoing neurotoxin injections. The study hypothesizes that pallidal neurostimulation is more effective in controlling CD symptoms than BoNT treatment and that is safe in this indication, too.

### Visit schedule

To provide a fair comparison between the two treatments with time varying efficacy, we took special care in scheduling the study visits. Baseline visit takes place 6 weeks after operation. This interval was chosen to reduce the impact of the surgical stun effect of electrode implantation. Additionally, motor symptom control efficacy is evaluated in FU1 and FU3 (each 4 weeks after BoNT injection), when the neurotoxin treatment effect is supposed to be maximal [6].

### Quality management

In order to maintain comparable and highest treatment standards at all study sites, we only recruited DBS centres operating more than 25 patients within a year. All 11 participating sites are university hospitals in Germany with a longstanding experience in DBS and a BoNT outpatient clinic run by an expert physician (board certified neurologist and special experience in neurotoxin treatment).

Furthermore, we provide a controlled rating training for TWSTRS score to increase inter-rater-reliability. To reduce possible bias trough changing or different examiners, a standardized video recording is scheduled at RAN, FU4 and FU5 to enable a central evaluation of symptom severity.

### Blinding

Two independent teams at each site are established to guarantee that the study could be performed in a blinded fashion. The BoNT reconstitution process must be conducted by an unblinded team member. Provided in neutral syringes, solutions of BoNT or saline are not distinguishable from each other, as both having no special colour or smell.

DBS settings are mandatory to be implemented with stimulation amplitude of 0.5 V below the threshold of possible adverse effects, which was tested before during monopolar review process. This should ensure that patients are not able to perceive switch-on of DBS system.

### Summary

To the best of our knowledge, StimTox-CD is the first randomized, double-blind and controlled comparison of DBS and BoNT in CD. As described, the study protocol is designed to answer the question which therapy method is more effective in controlling motor symptom severity and provides better outcomes concerning disease-related disability and quality of life. The fact that patients will be included in this trial, which have a partial but not satisfactory treatment effect of neurotoxin injections, addresses the unmet medical need of alternative treatment strategies for this less disabled CD population. A positive study outcome would have impact on treatment guidelines for CD. On the condition that DBS proves to be safe in this indication, physicians might be able to offer DBS earlier in the course of CD and empower patient treatment choices.

## Abbreviations

AE: adverse events
BDI: Beck Depression Inventory
BoNT: botulinum neurotoxin
BPRS: Brief Psychiatric Rating Scale
CD: cervical dystonia
CDQ-24: Craniocervical Dystonia Questionnaire
DBS: deep brain stimulation
EQ-5D: Euroquol (life quality questionnaire)
EVA: Evaluation visit
FU: Follow up visit
GDRS: Global Dystonia Rating Scale
GEE: Generalized estimating equation
GPi: Globus pallidus internus
ITT: Intention-to-treat population
MCI: Mild cognitive impairment
MDRS: Mattis Dementia Rating scale
PD: Parkinson’s disease
PP: per protocol population
RAN: randomization visit
SCR: screening visit
SD: standard deviation
SF-36: Short Form 36 (life quality questionnaire)
TWSTRS: Toronto Western Spasmodic Torticollis Rating Scale
